### Participant timeline {13}

The participant timeline is shown in Table 1.

### Sample size {14}

We are going to recruit 42 participants (21 participants per arm). The total sample size has been calculated using G*Power 3.1 Software to test an effect size of 0.25 with a power (1−*β*) = 0.8 for a sample with two independent groups (taVNS vs Sham-taVNS) and 4 dependent measures (PANAS-N score post-induction for neutral, funeral, sex-assault and domestic violence videos). The sample size needed is *n* = 34, calculated with an alpha level of 0.05. With an expected level of attrition of about 20%, the sample size has been increased by a factor of 1/(1–0.2) = 1.25 or 25% to 42 subjects.

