### Outcomes {12}

The primary outcome will be the change in negative emotional arousal from baseline, assessed immediately after the affect-induction procedure (post-induction ratings) using the PANAS. Negative emotional arousal will be measured through self-reported ratings of negative emotions on the PANAS (PANAS-N) at five time-points: baseline, after the neutral video, and after each of the three affect-inducing videos (designated as t1, t3, t4, t6, and t8 in Table 1). The means of the PANAS-N scores for each time point will be calculated and used to test the null hypothesis of no difference between the taVNS and sham taVNS groups. A mixed model analysis will be employed to assess each time point separately, ensuring comprehensive evaluation across all time points. The PANAS-N scores have already been used to measure the emotional arousal in previous studies using the same affect induction procedure with BPD patients and have been shown to be able to detect within and between groups differences [28]. The GSR recording, a physiological measure of emotional arousal, will be performed throughout the entire procedure and used to validate the PANAS-N data.

Since an increased emotional reactivity/intensity, one of the three components of the emotional vulnerability together with emotional sensitivity and longer emotional recovery time, is central in the physiopathology of BPD and the underpinning for many of the related symptoms and dysfunctional behaviors (e.g., self-harm) [5], to test the effect of taVNS on this primary outcome may have direct clinical utility. The available psychological treatments are associated with an improvement in the emotional regulation of BPD patients but have uncertain effects on the underlying emotional vulnerability [33].

The secondary outcomes of the study include:Change in negative emotional arousal from baseline at prior to affect induction (pre-induction ratings) as assessed by PANAS.Change in negative emotional arousal from immediately after affect-induction at 4 min after affect induction (recovery ratings) as assessed by PANASPerceived effectiveness in managing emotions (PEME) scores (0–9) during affect induction.

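### The stated 80% power at n = 34 does not hold for the per-time-point taVNS versus sham comparison, which has about 29% unadjusted; it fits an unadjusted four-rating average only if a person's ratings are uncorrelated

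*Protocol article*

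**What the plan says.** Protocol article, Sample size {14}: "The total sample size has been calculated using G*Power 3.1 Software", "to test an effect size of 0.25 with a power (1−*β*) = 0.8", for "two independent groups (taVNS vs Sham-taVNS) and 4 dependent measures (PANAS-N score post-induction for neutral, funeral, sex-assault and domestic violence videos". The result is given as "The sample size needed is *n* = 34, calculated with an alpha level of 0.05". Recruitment is set higher to allow for attrition: "We are going to recruit 42 participants (21 participants per arm". The section does not name the G*Power routine, the effect-size index, or the correlation assumed among the four ratings.

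Protocol article, Outcomes {12}: the primary outcome is change in PANAS-N from baseline, rated at t1, t3, t4, t6 and t8. The null hypothesis is that taVNS and sham do not differ. On how it is tested, the section says: "A mixed model analysis will be employed to assess each time point separately".

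Protocol article, Statistical methods {20a}: mixed models with a random effect for individuals. Group, treatment state and time are fixed effects, and baseline covariates are to be considered.

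**The concern.** The power statement and the primary hypothesis describe different comparisons. The calculation draws on four ratings per person, whereas a test at a single time point uses one. Even for a test that pools the four ratings, the gain from pooling depends on how strongly one person's ratings agree, and no value is given.

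This is the only power claim for the primary outcome. If the deciding test has well under 80% power, a null result could be taken as evidence against taVNS in BPD when the test was more likely than not to miss the effect assumed at the planning stage.

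**Working it through.** **Inputs from Sample size {14}:** effect 0.25, alpha 0.05, power 0.80, two equal groups, m = 4 ratings, N = 34 before attrition, 42 recruited.

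**Assumptions:** 0.25 is Cohen's f, the usual index for G*Power's ANOVA routines, so d = 2 × 0.25 = 0.5. The correlation ρ among one person's ratings is not stated, so it is varied. All power figures come from the noncentral F distribution.

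**1. Reproducing n = 34.** For the between-group test averaged over m ratings, λ = f²·N·m / (1 + (m − 1)ρ), with df 1 and N − 2. At ρ = 0 and N = 34, λ = 0.0625 × 34 × 4 = 8.5 and power is 0.807. At N = 33 it is 0.795. The stated figure therefore reproduces exactly, but with the four ratings treated as independent.

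**2. The same test with correlated ratings.**

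| ρ | λ at N = 34 | Power at 34 | N for 80% (equal arms) |
|---|---|---|---|
| 0 | 8.50 | 81% | 34 |
| 0.1 | 8.5/1.3 = 6.54 | 70% | 44 |
| 0.3 | 8.5/1.9 = 4.47 | 54% | 62 |
| 0.5 | 8.5/2.5 = 3.40 | 43% | 82 |
| 0.7 | 8.5/3.1 = 2.74 | 36% | 100 |

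**3. The group-by-measure interaction.** λ = f²·N·m / (1 − ρ), with df m − 1 and (N − 2)(m − 1). With m = 4 this gives N = 24 at ρ = 0.5. It gives 34 for ρ of about 0.26 to 0.29, or at ρ = 0.5 with a sphericity correction ε = 0.6. None of these settings is stated.

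**4. One time point, as in Outcomes {12}.** With m = 1, λ = f²·N and no ρ among the ratings is needed.
- N = 34: λ = 2.125, power 29%.
- N = 42: λ = 2.625, power 35%.
- 80% power needs N = 128.

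Adjusting for a baseline score with correlation r to the outcome divides the variance by 1/(1 − r²), so λ = f²·N / (1 − r²):

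| r | Power at 34 | Power at 42 |
|---|---|---|
| 0.5 | 37% | 45% |
| 0.7 | 51% | 60% |
| 0.8 | 65% | 75% |

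No entry reaches 80%.

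**5. A single pooled contrast:** the mean of the three negative-video ratings, adjusted for t1, with d = 0.5 and a common correlation ρ among t1 and the three ratings. The variance factor is v = (1 + 2ρ)/3 − ρ², and λ = f²·N / v.

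| ρ | v | Power at 34 | Power at 42 |
|---|---|---|---|
| 0.3 | 0.443 | 56% | 66% |
| 0.5 | 0.417 | 59% | 69% |
| 0.7 | 0.310 | 72% | 81% |
| 0.8 | 0.227 | 84% | 91% |

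With baseline adjustment, higher correlation raises power over this range, the reverse of step 2.

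**The case against.** The strongest reply is that n = 34 does come out of the between-group formula. A reader might infer that the sponsor powered a different test, but the article does not show which routine was run, and at ρ = 0 the between-group routine gives 34. The inputs may stand in the full protocol, which is not shown, so their absence from the article is not in itself the fault. This stands. The fault is that the stated power does not match the per-time-point comparison and fits the unadjusted average only under a correlation at odds with the article's own model.

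A reader might also take 43% as the trial's power. That figure requires ρ = 0.5, which appears nowhere in the article, and it ignores baseline. Since the outcome is a change from baseline and baseline covariates are to be considered, an adjusted average does better: step 5 reaches 81% at ρ = 0.7 with all 42 analysed. So it is not established that the trial cannot reach 80% for any sensible contrast.

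A difference in change from baseline can also be modelled as a group-by-time effect, so an interaction is not excluded. But Outcomes {12} does not state one as the hypothesis, and the interaction yields 34 only with unstated settings.

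Finally, 0.25 could be another index. Read as f² (f = 0.5), a single comparison would have 80% power at 34, but then the four dependent measures listed in the calculation would play no part.

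**Conclusion.** The concern holds in this form: the stated 80% does not apply to the test at each time point. That test has about 29% power at 34 completers and 35% at 42 unadjusted, and stays below 80% with a baseline covariate correlated up to 0.8 (65% and 75%). These figures rest on reading 0.25 as Cohen's f and on two-sided alpha 0.05; the adjusted ones also rest on the assumed baseline correlation.

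For an unadjusted average of the four ratings, 80% at 34 requires essentially uncorrelated ratings from the same person in one session. That sits badly with a model chosen because ratings within a person go together. At any clearly positive correlation the power is lower, by an amount the article does not allow one to fix.

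The documents do not support saying that the wrong test was powered, that the true power is 43%, or that 42 participants are too few for every reasonable primary contrast.

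**What to change.** In Sample size {14} and Outcomes {12}, name one contrast that decides the primary hypothesis and restate the power for it, giving the effect-size index, the assumed correlation and whether baseline is adjusted for. One candidate is the mean of the three negative-video PANAS-N ratings (t4, t6, t8) adjusted for t1, with power reported over a range of correlations as in step 5. Present the comparisons at individual time points as supportive, with their own lower power.

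The cost is wording in the protocol and analysis plan, and no extra patients are needed. The stated power becomes less favourable unless a high correlation can be justified. The article expects recruitment to run into 2025, so the change can be made before analysis.

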## Recruitment {15}

The participants will be recruited among those having an ongoing contact or discharged from a psychiatry department in Sweden. The presence of a dedicated outpatient unit for personality disorders within the department of psychiatry for affective disorders at Sahlgrenska University Hospital in Gothenburg, with circa 1000 ongoing patients, is expected to speed up the recruitment process to reach the target sample size. Potential candidates will be referred to the study team by their healthcare providers or recruited on a voluntary basis by on-site advertisements. The interested candidates will be contacted by the investigator over the phone to be informed about the study nature, to evaluate the potential interest in participating in the study, and to preliminarily evaluate their eligibility. A copy of the informed consent will be sent via e-mail, by ordinary mail, or given on-site to the participants to give them time to read it before being invited to the laboratory and make a final decision about their eventual participation in the study.

## Assignment of interventions: allocation

### Sequence generation {16a}

The computerized random number generator is used to generate random sequences on a 1:1 basis. The random sequence will be put into a sealed, opaque, and sequentially numbered envelope by a team member not involved in the enrolment and investigation procedures. When the participant is admitted to the operating room the investigator will sequentially open the envelopes, based on their numbered order, to obtain a random sequence to determine the grouping. Participants with random sequences 1–21 are assigned to group taVNS, while 22–42 are assigned to group sham taVNS. Each participant will be given a unique study sequential number on the envelope cover in the order of their participation in this study. The random sequences of all participants and their corresponding study sequential numbers will be recorded.

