After the baseline assessment has been completed, the transcutaneous electrical vagus nerve stimulation, delivered through a taVNS device (tVNS® R - tVNS technologies, Germany), will start. First, the taVNS device will be described and the taVNS electrode positioned at either the ear concha (active taVNS) or ear lobe (sham taVNS). The device consists of a stimulation unit and an ear electrode that is worn like an earphone. The stimulation unit sends electrical impulses through the electrode, which stimulates a branch of the vagus nerve transcutaneously (through the skin) in the auricle. The device can stimulate at an intensity between a minimum of 0.1 mA to a maximum of 5.0 mA with a biphasic waveform, an impulse duration of 28 s on and 32 s off, and an impulse frequency of 25 Hz. The stimulation intensity will be adjusted for every subject gradually by 0.1 mA at time until a tingling sensation or pulsation can be felt at the stimulation location. The stimulation should be clearly noticeable but not painful or uncomfortable. The device is CE-marked, indicating conformity with European Union regulations for medical devices, for the following conditions: anxiety, asthma, atrial fibrillation, autism, cognitive impairment, Crohn’s disease, depression, epilepsy, fibromyalgia, inflammation, migraines, Parkinson’s, Prader-Willi yndrome, sleep disorders, stroke, tinnitus. However, it is important to clarify that while the device has obtained CE marking, it has not received approval from the FDA or the EMA for the treatment of the listed conditions.

Four minutes after the optimal stimulation dose has been reached, the affect induction procedure will start. The affect induction procedure that will be used in this trial was developed by Daros and colleagues [71]. It has been shown to be tolerable and able to evoke higher negative emotional arousal in BPD patients in comparison with healthy controls [71]. It consists in the presentation on a computer screen of four (one neutral and three affect evoking) 4-min-long videos in sequence, each of which is followed by a 4-min post-induction period during which participants will rate the quality and intensity of the emotions perceived (PANAS) (post-induction ratings) and the perceived effectiveness in managing their emotions (PEME) [32].

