### Criteria for discontinuing or modifying allocated interventions {11b}

Each participant has the right to withdraw from the study at any time. In addition, the investigator may discontinue a participant from the study at any time if the investigator considers it necessary for any reason, including ineligibility (either arising during the study or retrospective having been overlooked at screening), significant protocol deviation, significant non-compliance with study requirements, an adverse event which requires discontinuation of the taVNS or results in inability to continue to comply with study procedures, emotional crisis which results in inability to continue to comply with study procedures or consent withdrawn.

The reason for withdrawal will be recorded in the electronic Case Report form (eCRF) (Qualtrics module) and in a research note in the patient research diary. If the participant is withdrawn due to an adverse event, the investigator will arrange for follow-up visits or telephone calls until the adverse event has resolved or stabilized.

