### Concealment mechanism {16b}

The use of opaque sealed envelopes will ensure concealment until the interventions are assigned.

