### Implementation {16c}

A member of the research team not involved in the enrolment and investigation processes will generate the allocation sequence using a computer program and seal it in opaque envelopes. The envelopes will be handed over to the investigator who will open them according to the unique sequential number on the envelope at the intervention allocation.

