### Data management {19}

eCRF entries will be considered source data since the CRF is the site of the original recording (e.g., there is no other written or electronic record of data). In this study, the Qualtrics Survey module will be the eCRF and will be used as the source document for the anamnestic information collected at the screening and for all the assessments and evaluations.

All study data will be entered on the online Qualtrics Survey. Data will be protected in accordance with the “Qualtrics Security statement” (SOC 2 Type II Certification, ISO 27001, 27017, and 27018 Certifications, FedRAMP Authorization, HITRUST), and access available only to the research group. The data will be stored in the online Qualtrics Account owned by to the Principal Investigator (PI) and protected by a unique password.

The participants will be identified by a unique sequential study-specific participant ID number and a unique randomization code. These two numbers will be recorded in the participant module in the IMotions software [32] and on the first page of the online Qualtrics Survey [31]. The name and any other identifying detail will NOT be included in any study data electronic file and no key between participant ID number, name, or other information that could identify the participant will be used. The data recorded in the IMotions software will be stored off-line in a dedicated computer, protected by a password that only the PI has access to.

All the other documents (informed consent, envelope with participant number and randomization code, MINI, and SCID 5 PD) will be stored in a locked cupboard at the lab accessible only to the PI. On all study-specific documents, other than the signed consent, the participant will be referred to by the study participant number/code, not by name.

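### The envelope is opened before the baseline rating, and a code that appears to reveal the arm is recorded on the first survey page and in the sensor software

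*Protocol article*

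**What the plan says.** All places are in the protocol article.

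- **Opening of the envelope.** Sequence generation {16a}: "When the participant is admitted to the operating room the investigator will sequentially open the envelopes". Implementation {16c} gives a second, looser description, in which the investigator will "open them according to the unique sequential number on the envelope at the intervention allocation". Concealment mechanism {16b} adds: "The use of opaque sealed envelopes will ensure concealment until the interventions are assigned".
- **Meaning of the number.** Sequence generation {16a}: "Participants with random sequences 1–21 are assigned to group taVNS, while 22–42 are assigned to group sham taVNS".
- **Where the code is kept.** Data management {19} gives each participant a study number and a randomization code. Both are entered in the participant module of the sensor software and "on the first page of the online Qualtrics Survey".
- **When the arm is used.** Intervention description {11a} seats the participant, attaches the ECG and skin-conductance sensors and collects the baseline PANAS. Electrode positioning at concha or lobe comes next: "After the baseline assessment has been completed, the transcutaneous electrical vagus nerve stimulation" begins.
- **Who knows the arm.** Who will be blinded {17a}: participants only. Under {11a} an investigator or assistant stays beside the participant throughout the session.
- **Role of t1.** Outcomes {12} defines the primary outcome as change in PANAS negative affect from baseline. The first secondary outcome, t1 to t2, uses the same baseline.

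**The concern.** A baseline rating is best taken while nobody in the room knows the arm. Randomisation then makes any baseline difference between arms a matter of chance. Here the person who has just learned the arm sits next to a participant who has yet to give t1, although nothing in the procedure requires that knowledge so soon. If manner, remarks or the handling of the set-up differed by arm, t1 could shift, and with it the primary change score and the t1-to-t2 secondary outcome.

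The second issue is the identifier. If the recorded code is the number from the envelope, the arm can be read from it with a one-line rule, and that rule is printed in an open article published in June 2024 while recruitment is expected to run to September 2025. The code then travels with the survey record and the sensor record. If the first page is shown on the participant's screen, it is also in the participant's sight. This is an avoidable weakness in a trial whose only blinded party is the participant.

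**Working it through.** The plan gives no figure to reproduce on this point. The check is of the order of events and of what the code means.

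**1. Order of events as written**

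1. Consent, then screening at the laboratory before the study procedure starts (Screening, under {18a}). Its order relative to the envelope is not stated.
2. Admission to the room; envelope opened ({16a}). This reads the operating room named there as the room where the session is run.
3. Code entered on page one of the survey ({19}). The same survey holds the screening history and the baseline and later ratings ({18a}), so in page order this entry precedes t1.
4. Sensors attached and t1 PANAS collected ({11a}).
5. Electrode placed at concha or lobe; stimulation adjusted and started ({11a}).
6. t2 and all later ratings.

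The arm is known from step 2 and first needed at step 5. The t1 rating at step 4 lies in between.

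**2. Does another section move the opening later?** {16c} ties opening to the allocation of the intervention but does not place that moment relative to t1. If it means electrode placement, it conflicts with {16a}; if it means room entry, it repeats {16a}. {16b} protects concealment only up to assignment, which under {16a} is room entry. Neither puts the opening after t1.

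**3. Does the code show the arm?** The numbers 1–21 are 21 values and 22–42 are 42 − 21 = 21 values, together 42 at 1:1. The rule is fixed: 21 or below is taVNS, above 21 is sham. That the randomization code in {19} is this number is an inference. It is supported by {19} itself, which lists among the stored papers an envelope carrying the participant number and the randomization code. If the code is some other, uninformative string, this part of the point falls away.

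**4. How a shift in t1 would enter the result.** Let Y be a post-induction score, B the t1 score, and δ a between-arm difference in B caused by knowledge of the arm, with Y itself unaffected.

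- Unadjusted change: difference in mean (Y − B) = difference in mean Y − δ. The effect moves by the full δ.
- With B as a covariate with slope b: the effect moves by b × δ.

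The documents give no value for δ or b and no standard deviation for the PANAS negative-affect score, so no size can be computed.

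**The case against.** The strongest reply is that t1 is hard to influence. It is a self-report by a participant meant to be blinded, made on locked, timed, auto-advancing pages, with the staff member quiet and outside the participant's line of sight. The investigator does not score it. The same unblinded person is present for every later rating in any case, so the added exposure at t1 is modest. This stands, and it limits the likely size. It does not explain why the arm should be known before t1.

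A participant who decodes the number would have to see it, have read the article and recall the rule. That is remote. The article already concedes a more direct route to unblinding, through knowledge of the electrode sites. This also stands.

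A reader might infer several stronger points that the documents do not support:

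- **Eligibility is decided with the arm known.** Screening is placed before the study procedure, and {16b} and {16c} are compatible with allocation after screening. The order is not stated, and Table 1, which may fix it, is not reproduced.
- **Early opening makes withdrawals selective.** {11b} does allow discontinuation for "ineligibility (either arising during the study or retrospective having been overlooked at screening", among other reasons. But the investigator knows the arm from electrode placement onward whenever the envelope is opened. That is a feature of the declared single-blind design, and later opening would not change it.
- **A masked analysis is impossible.** The field can be recoded or removed before the data reach the analyst. The article claims no analyst masking, and such detail may sit in an analysis plan that is not shown.
- **The baseline is no longer protected by randomisation.** Allocation remains random ("The computerized random number generator is used to generate random sequences on a 1:1 basis"). Bias would require cues that actually change a self-rating.

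**Conclusion.** The point holds in a limited form. As written, the unblinded investigator learns the arm before the rating that anchors the primary outcome, and an identifier that appears to reveal the arm is entered in both data systems. The first part follows directly from {16a} and {11a}. The second rests on the inference that the randomization code is the number in the envelope.

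The effect on t1 is probably small and cannot be quantified. It is tempting to assume a shift of some fraction of a standard deviation and set it against the planned effect. That would rest wholly on assumed values: the article gives no such shift, and Sample size {14} states an effect size of 0.25 without naming the effect-size measure or the test. The procedure as described applies to all 42 planned participants, but that counts who passes through it, not how much bias results.

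This is an inexpensive improvement to make for the rest of recruitment, not a threat to the trial's validity.

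**What to change.** For participants still to be enrolled:

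- State in {16a} and {16c}, in the same words, that the envelope is opened only after eligibility is signed off and the t1 PANAS is submitted, immediately before electrode placement. This also settles the unstated order relative to screening.
- Amend {19} so that only the sequential study number goes on the survey's first page and into the sensor software. Keep the arm-revealing code in a separate log, linked by study number.

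The cost is a changed step order and one survey field. No extra staff are needed, and sample size and stimulation procedure are unaffected. The change cannot be applied to participants already enrolled, so the report should say from which participant it took effect.
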